## Abstract

**Introduction:**

The efficacy of interventions based on mindfulness and compassion has been demonstrated in both clinical and general population, and in different social contexts. These interventions include so-called attentional and constructive meditation practices, respectively. However, there is a third group, known as deconstructive meditation practices, which has not been scientifically studied. Deconstructive practices aim to undo maladaptive cognitive patterns and generate knowledge about internal models of oneself, others and the world. Although there are theoretical and philosophical studies on the origin of addiction to the self or on the mechanisms of action associated with the deconstruction of the self, there are no randomized controlled trials evaluating these techniques in either a healthy population or clinical samples. This study aims to evaluate the effect of three deconstructive techniques by comparing them to mindfulness in the general population.

**Methods and analysis:**

A randomized controlled clinical trial will be conducted with about 240 participants allocated to four groups: (a) mindful breathing, (b) prostrations, according to Tibetan Buddhist tradition; (c) the Koan Mu, according to Zen Buddhist tradition; and (d) the mirror exercise, according to Toltec tradition. The primary outcome will be the qualities of the non-dual experience and spiritual awakening, measured by the Nondual Embodiment Thematic Inventory, assessed at pre- and post-treatment and at 3- and 6-month follow-ups. Other outcomes will be mindfulness, happiness, compassion, affectivity and altered state of consciousness. Quantitative data will be compared using mixed-effects linear regression models, and qualitative data will be analysed through thematic analysis and using the constant comparative method from grounded theory.

**Ethics and dissemination:**

Approval was obtained from the Research Ethics Committee of Aragon, Spain. The results will be submitted to peer-reviewed specialized journals, and brief reports will be sent to participants on request.

**Trial registration:**

ClinicalTrials.gov NCT05317754. Registered on August 2,2022.

## Background

According to Kabat-Zinn [1], “mindfulness is the practice of purposely bringing one’s attention to experiences occurring in the present moment without judgment”, a skill that can be developed through attentional meditation. Since he started to teach mindfulness in 1979 at a hospital associated with the University of Massachusetts, mindfulness has demonstrated efficacy for increasing psychological and physical well-being in healthy adults in general [2], and in specific environments such as clinical settings [3], the workplace [4] and schools [5, 6].

In the early years of the twenty-first century, another kind of meditative technique, known as compassion, emerged in the West. Goetz et al. [7] defined compassion as the feeling that arises when witnessing another’s suffering and motivates a subsequent desire to help. Systematic reviews and meta-analyses indicate that compassion has an important role to play in the treatment of disorders such as depression and anxiety and the improvement of well-being in healthy individuals [8–10].

The large number of meditation types and the great differences that set them apart led authors such as Dahl et al. [11] to develop a now widely used classification, based on cognitive neuroscience and clinical psychology, which comprises three groups of meditation types:Attentional meditations. These types train a variety of processes related to the regulation of attention, with mindfulness being the best-known type in this group. The authors propose that a shared characteristic of all these meditation practices is the systematic training of the capacity to intentionally initiate, direct and/or sustain these attentional processes while strengthening the ability to be aware of the processes of thinking, feeling and perceiving.Constructive meditation. These types include a variety of meditation practices that strengthen psychological patterns that foster well-being. In contrast to attentional practices, which often focus on simply monitoring cognitive and affective patterns, constructive meditation involves systematically altering the content of thoughts and emotions. Compassion would be the most widely studied technique within this group.Deconstructive meditation. These types aim to undo maladaptive cognitive patterns by exploring the dynamics of perception, emotion and cognition, and by generating insights into one’s internal models of the self, others and the world. The authors suggest that a central mechanism in this kind of meditation is self-inquiry, which is the process of investigating the dynamics and nature of conscious experience.

In contrast with the great amount of scientific research on attentional and constructive meditations, deconstructive meditation types have received little attention from neuroscientists [12]. This is surprising, given that deconstruction of the self forms the core of meditative practices in a number of major Eastern contemplative traditions, such as Buddhism, Vedanta Advaita and Taoism [13]. In fact, there is a trend away from the stringent frame of mindfulness and meditation to a wider concept of contemplative sciences [14], in which deconstruction of the ego would be one of the most important goals.

Moreover, evolutionary social psychology has also shown concern for the fact that human beings have an evolved capacity for self-awareness, along with a propensity to focus primarily on their own welfare. Although this focus has clear adaptive functions, such as physical preservation and self-regulation, this pervasive egoic mindset, in an increasingly crowded and interdependent world, is associated with high personal and societal costs. This is the basis of rising interest in hypo-egoic phenomena in psychology [15].

Despite the publication of a number of theoretical and philosophical papers on the origin of ego addiction [16] and the mechanisms of action associated with deconstruction of the ego [17, 18], no randomized controlled trials have been conducted to assess these techniques either in a healthy population or in clinical samples. This is the first exploratory randomized controlled trial to evaluate the effect of several different deconstructive meditation techniques on healthy individuals. Our hypothesis is that all four interventions would be effective for decreasing the ego perspective in the general population, and more specifically, that the three specific deconstructive interventions would be more effective than the control attentional mindfulness technique.

## Methods

### Study design

Participants will be randomly allocated to a four-armed randomized controlled clinical trial with four conditions: (a) standard mindfulness alone, using the mindful breathing technique mindfulness of breathing, which will be considered the control condition; (b) prostrations, according to Tibetan Buddhist tradition; (c) the Koan Mu, according to Zen Buddhist tradition; and (d) the mirror exercise, according to Toltec tradition. They will be assessed at pre- and post-treatment and 3- and 6-month follow-ups. This study will conform to the Consolidated Standards of Reporting Trials (CONSORT) statement (http://www.consort-statement.org) [19] for reporting trials and the Standard Protocol Items: Recommendations for Intervention Trials (SPIRIT) guidelines [20] for clinical trial protocols. The study’s trial registration number is ClinicalTrials.gov NCT05317754.

### Study population, recruitment and eligibility criteria

This randomized controlled clinical trial will be conducted within the Master’s in Mindfulness programme and supervised by the Chair of Contemplative Sciences of the University of Zaragoza. Participants will be healthy adults recruited online from the general population of Spain and Spanish-speaking countries.

The participants will be recruited through several different social media (e.g. Twitter, Facebook and LinkedIn) and university newsletters (specifically, as part of the university’s Master’s in Mindfulness programme). When participants contact the research team, the study will be explained by one of the researchers, and if they agree to participate, an informed consent form containing the main aim of the study, the name of the study leader and contact details will be provided. In order to prevent a high dropout rate, the research team will emphasize that once the study is completed, participants will be able to access the other study interventions, as well as being able to request a report with the results of the study.

Participants will subsequently undergo a clinical interview and fill out the paper-and-pencil screening survey describing their sociodemographic and clinical characteristics. This first data collection and screening step will be performed by specially trained psychologists for the purpose of assessing whether participants meet the eligibility criteria for inclusion in the study. When a participant is found to meet the inclusion criteria, an independent researcher will implement randomization by telephone to avoid predictability Flowcharts giving an overview of the study design and the study timeline are summarized in Figs. 1 and 2, respectively.

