**Fig. 2 Fig2:**
[figure not shown]
Schedule of enrolment, interventions and assessments

Inclusion criteria will be as follows: (a) older than 18 years of age; (b) no psychiatric diagnosis (self-reported); (c) more than 1 year’s experience of daily meditation practice, (d) having a computer and Internet connection at home; (e) being able to read and understand the Spanish language; and (f) willingness to participate in the study and sign the written informed consent form. Exclusion criteria include the following: (a) any diagnosis of a disease that may affect the central nervous system (pathological condition affecting the brain, traumatic brain injury, dementia) or other psychiatric diagnoses or acute psychiatric illnesses (severe range of depression, substance dependence or abuse, history of schizophrenia or other psychotic disorders, eating disorders), except for anxiety disorder; (b) any medical, infectious or degenerative disease that may affect mood; presence of delusional ideas; and hallucinations consistent or not with mood and suicide risk; and (c) taking any psychiatric medication.

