#### Sociodemographic data and meditation experience

Participants will be asked about their gender, age (in years), nationality, current city of residence, marital status (single, married, cohabiting couple, separated/divorced, widowed or other), education (undergraduate/bachelor’s degree/diploma, master’s degree, doctorate and others) and for information regarding their experience with meditation, such as whether they have had meditation experience in general (“yes” or “no”), the mean in minutes for each time that they practised formal meditation, length of meditation experience (i.e. less than 1 year, between 1 and 3 years, between 4 and 6 years, between 7 and 9 years, or more than 10 years), the time (in months) that they may have interrupted their formal practice during their lives, and the percentage of their time dedicated to each type of formal meditation (concentrative or focused attention, open monitoring, compassion/loving-kindness, values, deconstructive/non-duality and informal practice). A brief explanation of each type of meditation practice will be provided. In addition, an open field is included so that participants can indicate other meditative techniques that they practice and have not been explicitly collected. The meditation information provided and collected will be based on author recommendations and previous studies [11, 27].

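### The aim and hypothesis name the general population, but eligibility admits only people with more than one year of daily meditation

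*Protocol article*

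**What the plan says.** All references are to the protocol article.

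- **Abstract, Introduction:** "This study aims to evaluate the effect of three deconstructive techniques by comparing them to mindfulness in the general population".
- **Background, hypothesis:** the expectation is that "all four interventions would be effective for decreasing the ego perspective in the general population", with the three deconstructive techniques doing better than the mindfulness control.
- **Study population, recruitment and eligibility criteria, population statement:** "Participants will be healthy adults recruited online from the general population of Spain and Spanish-speaking countries".
- **Same section, recruitment channels:** social media and "university newsletters (specifically, as part of the university’s Master’s in Mindfulness programme").
- **Same section, inclusion criterion (c), printed after Fig. 2:** "more than 1 year’s experience of daily meditation practice".
- **Discussion:** the limitations list a potential lack of representativeness of the sample, without linking it to criterion (c).
- **Clinical implications:** possible benefit is projected to healthy populations and, more tentatively, to the prevention and treatment of disorders.

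The abstract does not mention criterion (c).

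**The concern.** The aim and hypothesis define the population about which the trial intends to draw inferences. Criterion (c) defines the population it can observe. The two differ on a characteristic close to both the intervention and the outcome: prior meditation practice, in a trial of meditation techniques scored on an inventory of non-dual experience.

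At stake is what the result may be said to show. A difference between arms, or the absence of one, in people who have meditated daily for more than a year gives no direct evidence about people who have not. A reader of the abstract alone would take the result to apply to the wider group.

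**Working it through.** No single figure decides this point. The one relevant figure is checked first, and then the passages are compared.

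**1. The plan's own figure.** *Sample size* gives 240 in total and 60 per arm, with a 5% level, 80% power, a between-arm difference of d = 0.5 at post-test and equal allocation. *Statistical analysis* makes the test two-tailed. With two time points, the group-by-time test is an F test on change scores with 3 and N − 4 degrees of freedom. When one arm differs from the other three by d, the noncentrality is

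λ = N × 0.25 × 0.75 × d² / [2(1 − ρ)],

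where ρ is the pre-post correlation. The article does not state ρ. Assuming ρ = 0.5 and putting in N = 240:

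λ = 240 × 0.1875 × 0.25 / 1 = 11.25.

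Under that assumption, 60 per arm is the smallest size that reaches 80% power, so N = 240 is reproduced. The result depends on the assumption: ρ = 0.4 gives N = 284 and ρ = 0.6 gives N = 192. A simple pairwise comparison at d = 0.5 gives 63 per arm, and 60 per arm has power 0.782. The population label does not enter any of these formulas. The article gives no NETI value by meditation experience, so any effect of criterion (c) on the assumed baseline of 65 cannot be calculated.

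**2. Stated target against actual sample.**

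| Place | Population |
|---|---|
| Abstract, aim | General population |
| Background, hypothesis | General population |
| Population statement | Healthy adults recruited from the general population |
| Inclusion criterion (c) | Only those with more than one year of daily meditation |

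**3. Can the statements be read together?** The population statement on its own could describe only the recruitment source, with eligibility applied afterwards. The abstract and the hypothesis cannot be read that way, because they state where the effect is to be evaluated and where it is expected to hold.

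**4. Does the limitation resolve it?** A potential lack of representativeness describes something that might happen during recruitment. Under criterion (c) the number of non-meditators and novices is zero in every arm, whatever happens in recruitment.

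**5. Size.** All 240 planned participants are experienced daily meditators. The share of evidence that comes directly from non-meditators or novices is 0 of 240.

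**The case against.** The strongest reply is that the article largely uses general population as the opposite of clinical. The abstract contrasts the two, and so does *Patient and public involvement*. Criterion (c) is stated openly, the Discussion mentions Western meditators when describing the qualitative study, the trial is called exploratory, and the implications are hedged. Enrolling experienced meditators is a legitimate choice.

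Much of this stands. The choice of sample is not at fault, and describing participants as healthy is accurate. But the non-clinical sense still leaves the aim and hypothesis naming a far wider group than the one enrolled, and the abstract gives no hint of the restriction.

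A reader might also infer more than the documents support:

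- **That the baseline form contradicts criterion (c).** *Sociodemographic data and meditation experience* asks "whether they have had meditation experience in general" and offers an answer of under one year. Table 1 places sociodemographic data at screening, and the screening survey is used to judge eligibility. A screening form needs answers that identify ineligible people, so this is no contradiction.
- **That the control arm is simply usual practice, so that any difference reflects novelty.** The article does not report what participants currently practise, and its form anticipates several types. *Interventions* gives all arms the same general instructions on daily practice time and allows only the assigned technique for 60 days. Resemblance to earlier practice is possible for some participants, but it is not established.
- **That the assumed control gain of 69 − 65 = 4 points is unjustified in such people.** It rests on cited studies that are not available here, so this cannot be shown. Setting that gain to zero would mean a deconstructive arm needs +6 rather than +10 to reach the planned difference of 75 − 69 = 6, a gain smaller by (10 − 6)/10 = 40%. Nothing in the documents supports a zero gain, and the calculation does not measure the population mismatch.

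**Conclusion.** The point holds as a mismatch between the stated target population and the eligible population. The trial can estimate effects in healthy adults with more than one year of daily meditation. It cannot directly answer its question for the general population, and the limitation as worded understates an exclusion that is built into the design.

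This is more than a clerical matter, because it determines what the trial may conclude, but its reach is limited. A reader might infer that the trial is biased or wrongly sized. It is not on this ground: the randomised comparison is internally valid for those enrolled, and neither the analysis nor N = 240 changes. The conclusion assumes only that criterion (c) will be applied as written. How far effects differ between experienced and novice meditators cannot be judged from the documents.

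**What to change.** Reconcile the abstract, the hypothesis and the population statement with inclusion criterion (c). If criterion (c) is intended:

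1. Name the target population in all three places as healthy (non-clinical) adults with more than one year of daily meditation practice.
2. In the limitations and *Clinical implications*, state that results do not directly apply to non-meditators or novices, and attribute this to the eligibility rule.
3. As a minor addition, use the baseline comparison of meditation experience already planned in *Statistical analysis* to show, by arm, the share of prior practice that was attentional. The form described under *Sociodemographic data and meditation experience* already collects percentage of time by type of practice. Readers could then judge how far the mindful-breathing control resembles what participants did before.

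The cost is a narrower stated claim, some rewording and one descriptive table row. No new data, analysis or participants are needed.

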**Fig. 1 Fig1:**
[figure not shown]
Study flowchart

**Fig. 2 Fig2:**
[figure not shown]
Schedule of enrolment, interventions and assessments

Inclusion criteria will be as follows: (a) older than 18 years of age; (b) no psychiatric diagnosis (self-reported); (c) more than 1 year’s experience of daily meditation practice, (d) having a computer and Internet connection at home; (e) being able to read and understand the Spanish language; and (f) willingness to participate in the study and sign the written informed consent form. Exclusion criteria include the following: (a) any diagnosis of a disease that may affect the central nervous system (pathological condition affecting the brain, traumatic brain injury, dementia) or other psychiatric diagnoses or acute psychiatric illnesses (severe range of depression, substance dependence or abuse, history of schizophrenia or other psychotic disorders, eating disorders), except for anxiety disorder; (b) any medical, infectious or degenerative disease that may affect mood; presence of delusional ideas; and hallucinations consistent or not with mood and suicide risk; and (c) taking any psychiatric medication.

### Sample size

The sample size estimation was based on testing whether the trend in the pre-to-post change would be different between the intervention groups. Firstly, we assumed that mindfulness practice would be able to present small pre-post effects on deconstruction of the ego, according to the previous studies on this subject [21]. For this reason, we assumed a common mean (SD) at baseline of 65 in the Nondual Embodiment Thematic Inventory [22], and a mean at post-test of 69 and 75 in the mindfulness group and the other deconstructive practices, respectively. This assumes a pre-post standardized difference in the mindfulness group of *d* = 0.3, a pre-post standardized difference in any of the other deconstructive practices of *d* = 0.8, and a post-test standardized difference between the mindfulness group and any of the other arms of *d* = 0.5, which corresponds to the average effect in some exploratory studies conducted by our group [23] and is aligned with the 0.5 standard deviation criterion considered clinically relevant [22]. Using a 1:1:1:1 ratio, assuming a 5% significance level and a statistical power of 80%, and applying the Hotelling-Lawley Trace approach for the general linear model, which supports the inclusion of baseline covariates and coincides with the Wald test for the general linear mixed model [24], we will need a total of 240 participants, and thus 60 subjects in each group.

### Randomization and blinding

Participants who meet the inclusion criteria for the study will receive a code from the screening assessors in order to preserve their confidentiality. An independent researcher unaware of the study characteristics will perform the randomization process. In order to randomly allocate the participants to one of the four previously described conditions, a computer-generated random number sequence (https://www.randomizer.org) will be used by means of a simple allocation strategy. After the participants are informed of the study characteristics, they will agree to participate before random allocation and without knowing the condition to which they will be allocated. The researcher who administers baseline assessments will be blind to the participants’ practice group. This researcher will be different from the one—also blinded—who administers the other measures throughout the study. Participants will complete all the measures online. Participants will not be blind to the intervention condition for practical reasons, but they will be blind at the time of the first assessment (pre-intervention). The person responsible for carrying out the data analysis will not know the type of intervention that each participant has carried out.

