### Statistical analysis

Descriptive data will be visually compared in terms of sociodemographic data, meditation experience and psychological variables across the arms at baseline to ensure balance among groups. They will be summarized using means (SDs) for continuous variables, and frequencies (percentages) for categorical variables. All analyses will follow a pre-specified plan. Outcomes will be compared between groups using the intention-to-treat principle. Missing outcome data (assumed to be missing at random) will be imputed using multiple imputations based on chained equations. The imputation model will include the outcomes at each time point, trial arm, the completion of the training and the extent to which meditation was practised, as well as other characteristics pre-specified for covariate adjustment, generating 20 imputed datasets. The primary analysis will be carried out for NETI total scores at post intervention. Outcomes at each time point will be compared using mixed-effects linear regression models. The main comparisons will be adjusted for baseline scores, gender and age. Means (SDs) will be reported for each trial arm along with the adjusted mean difference between arms, 95% confidence interval (95% CI) and *p*-value for the adjusted mean difference. Results from the complete-case analyses will be also reported, as well as additional sensitivity analyses utilizing complier-average causal effect (CACE)/instrumental variable methods to explore the causal effects of (a) participant engagement with the intervention and (b) regular meditation practice.

An alpha level of 0.05 will be established using a two-tailed test. The probability values relative to the main analysis will be adjusted according to Benjamini-Hochberg’s correction for multiple comparisons, but the secondary analyses will not be corrected.

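### Simple allocation of 240 people to four arms is valid but will rarely give 60 per arm and leaves meditation experience to chance; blocking and one more covariate are cheap gains in efficiency

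*Protocol article*

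**What the plan says.** Under Randomization and blinding, the protocol article states that a computer-generated random number sequence "will be used by means of a simple allocation strategy". It names no blocks, strata or minimisation for the trial. The stratification variables under Qualitative analysis concern only the interview and focus-group sample.

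The Sample size section rests on equal arms: "Using a 1:1:1:1 ratio, assuming a 5% significance level and a statistical power of 80" per cent, from which "we will need a total of 240 participants, and thus 60 subjects in each group".

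On covariates, the Statistical analysis section says: "The main comparisons will be adjusted for baseline scores, gender and age". The same section gives a visual comparison of baseline data, meditation experience included, as the means of making sure that the arms are balanced.

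Meditation history is collected in some detail under Sociodemographic data and meditation experience: length of experience in bands up to more than 10 years, and the share of practice given to each type, deconstructive practice among them. Entry requires more than one year of daily practice and sets no upper limit.

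**The concern.** Simple allocation makes the arms equal only on average. The planned comparisons with mindfulness all share the control arm, so a small control arm weakens all of them together. The sample size as stated has no slack to absorb this.

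Prior meditation experience could plausibly matter for a score of non-dual awareness, and the eligibility criteria admit a wide range of it. The protocol treats it as worth balancing, yet neither the allocation method nor the stated main model acts on it. Looking at a baseline table after allocation can describe an imbalance but cannot prevent or correct one. At stake are some precision and some protection against an awkward chance imbalance, both of which could be had at almost no cost.

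**Working it through.** **Inputs from the protocol article.** Total 240, planned 60 per arm, ratio 1:1:1:1, power 80% (Sample size). Two-sided test: "An alpha level of 0.05 will be established using a two-tailed test" (Statistical analysis). Effect: "a post-test standardized difference between the mindfulness group and any of the other arms of *d* = 0.5". Means: "a mean at post-test of 69 and 75 in the mindfulness group and the other deconstructive practices, respectively". The SD is not printed; a 6-point difference at d = 0.5 implies 6/0.5 = 12.

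**The plan's own figure.** I used a four-group F test (3 and 236 df) on standardised means 0, 0.5, 0.5, 0.5. The overall mean is 0.375, so the noncentrality is 60 × (0.375² + 3 × 0.125²) = 60 × 0.1875 = 11.25. Power is 0.806 with 60 per arm and 0.799 with 59. So 60 per arm is reproduced as the smallest size that reaches 80%, with no margin. This holds for post-test scores, or for change scores with an assumed pre-post correlation of 0.5; the article states no correlation.

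**Power of one comparison with control, 60 v 60 (normal approximation).** 0.5/√(2/60) = 2.739, and Φ(2.739 − 1.960) = 0.782.

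**Arm sizes under simple allocation (240 people, probability 1/4 each).**
- SD of one arm: √(240 × 0.25 × 0.75) = 6.7; 95% range 47 to 73.
- P(exactly 60 in each) = 240!/(60!⁴ × 4²⁴⁰) = 0.00027, about 1 in 3,700.
- Over 400,000 multinomial draws, the median smallest arm is 53 and the median largest about 68 (67 or 68, depending on the run).
- P(some arm has 50 or fewer) = 0.30. P(the control arm has 50 or fewer), from Binomial(240, 0.25), = 0.076.

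**Cost in precision.** The variance ratio against equal arms is (1/n₁ + 1/n₀)/(2/60).

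| Quantity | Equal arms | Simple allocation |
|---|---|---|
| Variance, a given control contrast | 1.00 | 1.013 on average |
| Variance, worst of three control contrasts | 1.00 | 1.07 on average; 1.17 at the 95th percentile |
| Power, a given control contrast | 0.782 | 0.777 on average; 0.720 at the 2.5th percentile |
| Power, four-group test | 0.806 | 0.803 on average; 0.727 at the 2.5th percentile |

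**Chance imbalance in experience.** The documents give no distribution, so I assume a two-level factor with 50% in each level and exactly 60 per arm. A difference of 15 points is 9 of 60. Conditioning on the control count and combining the three other arms as independent Binomial(60, 0.5), P(at least one arm differs from control by 9 or more) = 0.28. For one given comparison it is 0.12.

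**What an imbalance could do.** For a continuous measure of experience, the SD of the standardised difference between two arms is √(2/60) = 0.18. Assume experience correlates 0.1 to 0.3 with post-test score after adjustment for baseline. An imbalance of 0.2 to 0.36 SD then shifts a contrast by between 0.2 × 0.1 = 0.02 SD and 0.36 × 0.3 = 0.11 SD. At SD 12 that is 0.2 to 1.3 points, against a target of 6.

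**The case against.** The strongest reply is that nothing here is invalid. Simple allocation has an expected ratio of 1:1:1:1, 60 per arm is a planning target, and no stated analysis needs equal arms. It is also the least predictable method. All of that stands. A reader might infer that the allocation method contradicts the sample size or biases the comparisons; the documents support neither reading.

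A reader might also take 7% or 17% as the usual loss. Those figures are for the worst of three contrasts in each allocation. A given contrast loses about 1.3% in variance on average, and a loss of about 6 points of power for it comes only in the unlucky 2.5%.

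A third tempting reading is that experience is left unbalanced and wholly unadjusted. Randomisation balances it in expectation, and the standard errors already allow for chance imbalance. Adjustment for baseline score removes whatever part of its effect is already in that score. The documents give no evidence on how much remains, so the 0.1 to 0.3 above is an assumption. The article also refers to a pre-specified plan that is not shown, which may name more covariates.

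The missing margin belongs to the stated calculation as reproduced. Adjustment for baseline could recover power if the pre-post correlation is high enough.

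What remains is a stated method with a better alternative at almost no cost, and a statement about visual comparison that cannot be true as written.

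**Conclusion.** The point holds as a minor matter of efficiency. Simple allocation will rarely give 60 per arm, but on average it costs about half a percentage point of power for a given comparison with control (0.782 to 0.777) and slightly less for the four-group test (0.806 to 0.803). The loss reaches about 6 to 8 points only at the unlucky 2.5%. Experience is left to chance, with a 28% probability of at least one 15-point difference from control if the factor splits 50/50. The likely effect of such an imbalance is modest beside the 6-point target.

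The arm-size results rest only on the stated method and total. The power figures also rest on d = 0.5 without gain from baseline adjustment. They take the word simple at face value; if the sponsor meant a generator that returns sets of equal size, the article should say so, and the arm-size part falls away. The remark on visual comparison depends on none of these assumptions.

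**What to change.** 1. Replace simple allocation with permuted blocks of randomly varying size (for example 4 and 8), concealed, and released one at a time by the independent researcher who already allocates by telephone. Stratification by a two-level experience factor recorded before allocation is optional. A block of 8 holds two per arm, so one unfinished block leaves arms at most 2 apart, and one in each of two strata at most 4 apart.
2. Add length of meditation experience to the primary model alongside baseline NETI, gender and age, and state this before any outcome data are seen.
3. Reword the Statistical analysis section so that the visual comparison describes baseline balance and does not claim to ensure it.

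The cost is a new allocation list before recruitment starts, one more covariate from data already planned, and slight predictability at block ends, which varying block sizes and telephone release keep small.
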